### Trial design

In this three-arm feasibility trial, we will randomise eligible women (with depressive symptoms, functional impact and past-year IPV) to PST-IPV, standard PST or enhanced usual care (information about relevant sources of support). All arms represent additions to standard clinical care, which does not currently provide any routine interventions for perinatal depression or IPV.

This study is linked to a two-arm feasibility trial that will randomise eligible women (with depressive symptoms and functional impact) to standard PST or information only, the protocol of which is reported separately ([name], [name], [name], [name], [name], [name], et al. Brief problem-solving therapy for perinatal depression in rural Ethiopia: protocol for a randomised feasibility study.) (see Fig. 1).

**Fig. 1 Fig1:**
[figure not shown]
Flow diagram of problem solving therapy (PST) adapted for pregnant women experiencing intimate partner violence (IPV) feasibility trial procedure, indicating the relationship with a nested feasibility trial of standard PST in women not reporting past-year IPV (shaded grey). ANC antenatal care, HEW health extension worker, MINI Mini-International Neuropsychiatric Interview, PHQ-9 Nine-item Patient Health Questionnaire

## Methods

### Study setting

The study will be conducted in selected health facilities in the predominantly rural areas of Gurage zone (projected population 1,712,506) and Silt’e zone (projected population 1,043,242) in the Southern Nations, Nationalities, and Peoples’ Region of Ethiopia [51]. Primary health care is structured so that the nurse, midwife and health officer-run health centres (serving a population of 25,000–40,000) are linked to five community health posts (serving a population of 3000–5000) staffed by one or two health extension workers (HEWs) each, with access to a single primary hospital for more specialist care. HEWs, who have completed high school and received 1 year of undergraduate-level training [52], provide a first antenatal contact before referring women for further antenatal care (ANC) at a health centre or primary hospital and maintain contact with women during pregnancy.

This study builds on the programme for improving mental health care (PRIME) study [53], which integrated mental health into primary and maternal care in five LMICs, including the Gurage zone, Ethiopia [54]. In PRIME, a district-level mental health plan was developed in collaboration with key stakeholders and comprised interventions at the community, health facility and health system level. At the facility level, PRIME trained primary and maternal care staff using the mental health gap action programme (mhGAP) intervention guide of the WHO, which guides non-mental health specialists through clinical diagnostic and treatment algorithms for prioritised mental, neurological and substance use disorders [55]. The PRIME study investigators identified low detection rates of depression, which may be related in part to a lack of acceptable treatment options. Formative work was therefore conducted to inform adaptation of a brief psychological intervention for depression. In a nested study, PST was then adapted for antenatal women in this rural Ethiopian setting.

A systematic review and meta-analysis [21], further qualitative interviews and theory of change workshops ([name], [name], [name], [name], [name], [name], et al. Brief psychological intervention for antenatal depression: a qualitative study.) ([name], [name], [name], [name], [name], [name]. Adapting brief, task-shared problem-solving therapy for women experiencing intimate partner violence in rural Ethiopia: a qualitative study.) were then used to adapt this locally tailored PST intervention to address the needs and experiences of women affected by IPV. The preliminary theory of change visualises health worker perspectives on the components, hypothesised mediators, intermediate and long-term outcomes of PST-IPV intervention, and factors anticipated to influence the delivery and implementation of PST-IPV (see Supplementary file 1).

Adaptation for IPV focused on international guidelines [5], which recommend identifying women experiencing IPV, training health care providers about IPV, and providing woman-centred care and support when IPV is disclosed. PST-IPV will apply a PST approach in the context of IPV, enabling IPV-related problem solving and management of mental health-related symptoms.

### Participant sample size

As a feasibility trial, this study is not powered to detect intervention efficacy, but rather to estimate feasibility parameters to inform a future RCT, and test intervention and research protocols. With a total sample size of 75 (25 participants randomised to PST-IPV, 25 to PST and 25 to enhanced usual care), a drop-out rate of 30% can be estimated to within a 95% confidence interval of ±3%. To estimate the standard deviation of the primary feasibility outcome measure to inform a future RCT sample size calculation, recommended feasibility trial sample sizes range between a total of 24 and 50 across two arms [56, 57].

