### Participant reimbursement

All participants will be reimbursed for their time attending research interviews in addition to transport costs and any additional expenses incurred. Participants will be reimbursed for transport costs to attend PST or PST-IPV sessions but will not be compensated for their time during these sessions. This is to determine the acceptability of psychological intervention sessions to women and enable calculation of drop-out rates. A fund will be available to assist participants disclosing IPV who wish to access support services (for example. to facilitate transport to a government social support office or police station).

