### Intervention arms

Participants randomised to PST-IPV or standard PST will attend four intervention contacts within a maximum of 8 weeks. Where birth occurs before the end of treatment, the feasibility of continuing PST-IPV or standard PST post-natally will also be assessed.

Both manualised interventions will be delivered by trained health workers, such as nurses and midwives, supervised by Psychology Masters-level qualified research staff, with access to a project mental health professional for clinical concerns. Responses to concerns and risk incidents will follow standard operating procedures (SOPs). Government-employed health workers trained to deliver the interventions will be paid for their time.

Both PST-IPV and standard PST intervention arms follow the same structure of four sessions, based on the model successfully employed in South Africa and adapted for this rural Ethiopian setting [27, 66]. Session 1 focuses on basic psychoeducation, introduction to PST, identifying the most important things in the woman’s life and categorising problems into three groups. Session 2 focuses on revising session 1, coping strategies for ‘group A’ problems (which are upsetting but do not influence the most important things in the woman’s life) and the six-step problem solving method for ‘group C’ problems (which are important and can be solved). Session 3 focuses on revising session 2, coping strategies for ‘group B’ problems (which are important but cannot be solved) and psychoeducation about the phases of coping with bereavement and loss. Session 4 focuses on revising session 3, using problem solving skills in everyday life and reviewing how the coping strategies worked in practice. All sessions involve assigning and reviewing take-home activities.

PST-IPV content and materials are adapted to address the needs and experiences of women affected by IPV, whilst standard PST content and materials are generic. Adaptations for women experiencing IPV include training staff using content and materials from the new WHO curriculum on caring for women subjected to violence [67], attention to safety and sensitivity where women list IPV-related problems during sessions (including training with worked examples of problem solving focused on IPV), and adaptation of PST case studies to reflect common problems associated with IPV.

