### Statistical analysis

We will follow the Consolidated Standards of Reporting Trials (CONSORT) extension to randomised pilot and feasibility trials [83].

We will review process evaluation data for indications of sub-group differences in uptake, recruitment and retention of participants by site, health worker, recruitment method/site, participant (age, education level, religion, parity) and health worker characteristics (age, profession, years of experience). Quantitative scale results will be analysed using STATA [84].

Feasibility studies are not powered to calculate effect sizes but standard deviations and drop-out rates will be calculated on the intention-to-treat sample (all women who were randomised, regardless of uptake of the intervention) to inform sample size calculation for a future RCT, for outcome measures, recruitment rates and drop-out rates. Quantitative process data will determine future RCT design improvements, such as session number and duration, recruitment, outcome measures, and strategies preventing contamination. The extent of missing data will be evaluated as part of the process evaluation. For clinical outcome measures, missing data will not be imputed. Rather, standard deviations will be calculated using data from participants for whom outcome measures are available.

We will apply the framework approach to thematic analysis of qualitative interviews [85] and triangulate the results with quantitative process data through researcher meetings. The full descriptive analysis will include contextual barriers and facilitators influencing study outcomes.

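### The ±3% precision claimed for a 30% drop-out rate with 75 women should be about ±10 percentage points

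*Protocol article*

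**What the plan says.** The section on participant sample size describes the trial as "not powered to detect intervention efficacy, but rather to estimate feasibility parameters to inform a future RCT". It fixes the size and allocation, "With a total sample size of 75 (25 participants randomised to PST-IPV, 25 to PST and 25 to enhanced usual care", and in the same sentence says that "a drop-out rate of 30% can be estimated to within a 95% confidence interval of ±3" per cent. It gives no formula, finite-population correction or other denominator. The next sentence offers a second basis: published recommendations of 24 to 50 women in total across two arms for estimating the standard deviation of the outcome measure.

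The section on statistical analysis sets the denominator: "drop-out rates will be calculated on the intention-to-treat sample (all women who were randomised, regardless of uptake of the intervention". It names drop-out rates among the quantities that will inform the sample size of a future trial.

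Two other sections bear on what drop-out means. The one on participant reimbursement explains why women are not paid for time spent in therapy sessions: "This is to determine the acceptability of psychological intervention sessions to women and enable calculation of drop-out rates". The one on intervention arms confines sessions to two of the three arms: "Participants randomised to PST-IPV or standard PST will attend four intervention contacts within a maximum of 8 weeks". The enhanced usual care arm receives information only. The process evaluation section lists drop-out rates and follow-up rates as separate items.

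**The concern.** A half-width of 3 percentage points around 30% is far too narrow for 75 observations: one standard error alone is more than 5 points. In a trial that sets its size by estimation, the stated precision does the work that power does in an efficacy trial, so an error in it is an error in the design justification.

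What is at stake is the planning of the definitive trial. If drop-out is observed at 30% and the reader believes ±3 points, the true rate appears to lie between 27% and 33%. The inflation for attrition, 1 / (1 − rate), then runs from 1 / 0.73 = 1.37 to 1 / 0.67 = 1.49. With the correct Wald limits of 19.6% and 40.4% it runs from 1 / 0.804 = 1.24 to 1 / 0.596 = 1.68. A planner who relied on the stated figure would treat drop-out as much better known than it will be.

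**Working it through.** **Inputs.** From the section on participant sample size: n = 75 in total (25 per arm), p = 0.30, 95% confidence and a stated half-width of ±3%. From the section on statistical analysis: drop-out is calculated on all randomised women, so n = 75 is the right denominator for the stated claim.

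**Attempt to reproduce the stated figure.** The half-width for a single proportion is z × √(p(1 − p)/n).

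- Standard error: √(0.30 × 0.70 / 75) = √0.0028 = 0.0529.
- 95% half-width: 1.96 × 0.0529 = 0.1037, or ±10.4 percentage points.
- Interval: 30% ± 10.4 = 19.6% to 40.4%.
- Ratio to the stated figure: 10.37 / 3 = 3.46.

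The figure of ±3% is not reproduced.

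**Other methods at n = 75.** Wilson and Clopper-Pearson are evaluated at 22.5/75, which is exactly 30%.

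| Method | Half-width (points) |
|---|---|
| Wald, 95% | 10.4 |
| Wald with continuity correction, 95% | 11.0 |
| Wilson, 95% (20.8% to 41.1%) | 10.2 |
| Clopper-Pearson, 95% (20.0% to 41.7%) | 10.9 |
| One-sided 95% | 8.7 |
| 80% confidence | 6.8 |
| One standard error | 5.3 |

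**Other denominators (Wald, 95%, p = 0.30).** n = 100 gives ±9.0, n = 125 gives ±8.0 and n = 150 gives ±7.3 points.

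**What ±3 points would require.**

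- Sample size at 30%: 0.21 × (1.96 / 0.03)² = 896.4, so 897 women.
- Drop-out rate at n = 75: p(1 − p) = 75 × (0.03 / 1.96)² = 0.01757, so p is about 1.8%.
- Confidence level at n = 75 and p = 0.30: z = 0.03 / 0.0529 = 0.567, which is about 43%.

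**Relative reading.** If ±3% meant 3% of 30%, the half-width would be 0.9 points and the gap would be larger. A relative half-width of 10.4% would be 0.104 × 30 = 3.1 points, so a mix-up of relative and absolute error is one possible origin. The protocol does not say so, and the correction does not depend on it.

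**Secondary note: drop-out from sessions.** Sessions exist only in the PST-IPV and PST arms.

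- Both therapy arms pooled, n = 50: 1.96 × √(0.21 / 50) = 0.127, or ±12.7 points.
- PST-IPV alone, n = 25: 1.96 × √(0.21 / 25) = 0.180, or ±18.0 points.

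**The case against.** The best defence is that the error changes little. The trial is not powered for efficacy, and no progression threshold in the text depends on ±3%. Drop-out will be calculated from observed data, and its interval will have its true width whatever the sample size section predicted. No estimate is biased and no participant is affected. All of this stands. It limits the consequence, but it does not make the stated figure right.

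A second defence is that the shared control group described under strengths and challenges might enlarge the denominator. It does not help. The sentence ties the figure to 75 women, and even 150 would give ±7.3 points.

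Three stronger readings are tempting, and the document does not support them.

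- A reader might infer that the sample size has lost its only quantitative basis. It has not: the recommendation of 24 to 50 across two arms for the standard deviation stands independently, and any two arms here total 50.
- A reader might set ±18 points in PST-IPV against ±3 and say that precision is overstated sixfold (18.0 / 3 = 6.0). But the claim is made for all 75 women, the analysis section uses all randomised women, and the protocol states no precision for a single arm. The factor for the claim actually made is 3.46.
- A reader might want this protocol to settle which confidence limit the future trial should use to allow for attrition. That is a choice for another trial and corrects nothing here.

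**Conclusion.** The statement is wrong as written. For 75 women and a 30% drop-out rate the 95% half-width is about ±10 percentage points, not ±3, so precision is overstated by a factor of about 3.5. The result assumes only independent binary outcomes and the values of n, p and confidence level that the protocol gives. The choice of 95% interval method moves the half-width only between about 10.2 and 11.0 points.

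The point deserves correction because this is the only precision claim attached to 75 women and it concerns a parameter the trial is meant to supply to its successor. It gives no reason to change the sample size. The wider intervals for session drop-out are a fair secondary note, since the reimbursement section links drop-out to sessions, but they are not part of the arithmetic error.

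**What to change.** Keep 75 women and correct the one sentence, for example: *With 75 women randomised, the 95% confidence interval around a 30% drop-out rate would extend about 10 percentage points either side (roughly 20% to 40%).* Both figures come from the Wald method, so they agree with each other. Keep the term drop-out and the denominator of all randomised women, as in the section on statistical analysis.

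Optionally add: *Drop-out from therapy sessions would have a half-width of about 13 points over the two therapy arms (n = 50) and 18 points in PST-IPV alone (n = 25).*

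The cost is one or two sentences and a less favourable figure. No extra participants, visits or changes to conduct are needed. The trial status section gives this as version 1.0 with recruitment not yet begun, so the correction can go through the amendment route described there.

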### Participant recruitment

Research staff will consult health care workers based in primary hospitals and/or health centres in Gurage and Silt’e zones to identify potentially eligible women meeting those inclusion criteria about which information is held for screening. Potentially eligible women will be approached through ANC clinics and HEW home visits by research staff and provided with written and verbal information in Amharic, before being invited to give written, informed consent to initial screening. Non-literate women will signify their consent by finger print. A high school-educated assistant will act as a witness to confirm that the information sheet has been read aloud correctly to non-literate women. Women screened as eligible to participate in the randomised feasibility trial will then be invited to give written, informed consent to participate. As with screening, non-literate women will signify their consent to participate in the trial by witnessed finger print.

Due to potential risks of abusive partners learning of women’s involvement, information sheets, consent forms and other study paperwork will be kept in the locked research office after being read and signed but will be accessible to women at their request. Due to logistical challenges affecting women’s daily lives in this setting, it is not possible to give prospective participants 24 h to decide whether to take part. However, a minimum of 30 min will be allowed for the woman to make up her mind about participating in the study.

### Participant screening

Consecutive, potentially eligible women who provide informed consent will be screened for depressive symptoms and a history of past-year IPV after their ANC appointment. Depressive symptoms will be screened for using the locally validated [58] nine-item Patient Health Questionnaire (PHQ-9) [59]. To screen for IPV exposure, research staff will first read the introductory paragraph of the Amharic translated [60] Conflict Tactics Scale [61] to potential participants (or they may read themselves, if literate) to ameliorate stigma they may feel towards disclosing IPV. A five-item ‘non-graphic language’ screening test previously used in this and other LMIC contexts and found to be a valid measure of IPV [62] will then be administered. Finally, items from the WHO multi-country study [42] of women’s health and domestic violence, previously used in this setting, will be used to ask about experiences of IPV in the past year.

All screened women scoring five or more on the PHQ-9 [63, 64] and endorsing any functional impact of symptoms (the tenth item) will be invited to participate in the research study. Endorsement of the tenth item will be defined as answering “somewhat”, “very” or “extremely difficult” to the question “over the last two weeks, how difficult have these problems made it for you to do your work, take care of things at home, or get along with other people?”.

Consenting women who disclose any past-year IPV during screening will be randomised to one of PST-IPV, standard PST or enhanced usual care, whereas consenting women reporting no IPV on baseline measurements will be randomised to one of standard PST or enhanced usual care for the separate, nested PST feasibility trial (see Fig. 1).

### Participant recruitment procedures

All women screened as eligible to participate will be informed about the study and given the opportunity to ask questions before being invited to consent to participate in the randomised feasibility trial. Women consenting to participate will first receive their routine clinical care and then participate in a baseline interview using fully structured questionnaires. If screening or this assessment identify any sources of concern (e.g. suicidal ideation, risks to herself or others), the researcher will discuss these with the woman and explain the need to share them with her health care professional, before involving them. To be eligible to participate in the PST-IPV components of the overall study, women must meet the eligibility criteria (see below).

### Participant eligibility criteria

Women can be included if they:
Speak Amharic (the official regional language)Are aged 16 years or overAre between 12 and 34 weeks gestation of pregnancyAre intending to reside in the study area for the duration of the studyScore 5 or more on PHQ-9 with functional impairment (tenth question)Report IPV in the past year (in a current or previous relationship) during screeningConsent to participate, including to accept enhanced usual care or to attend four sessions of PST-IPV or PST (if randomised to a treatment arm)

Women are required to speak Amharic, the official language of the region, so that they can access all translated study materials, verbally or in writing. Relationships are defined as any romantic or sexual interaction within or outside marriage.

PHQ-9 has been validated in the study area in both primary care [63] and ANC attendees (area under the receiver operating characteristic curve 0.91, 95% confidence interval 0.86–0.96) [64]. For primary care attendees a score of five or more was the optimal cut-off for identifying possible depressive disorder. For antenatal women, a cut-off of four or more was optimal. However, since at the optimal cut-offs the positive predictive value was less than 50%, in this study women scoring above the cut-off (five or more) will be included if they also report difficulty in their day-to-day activities (measured using the PHQ-9 tenth item).

### Participant exclusion criteria

Women will be excluded if they:
Are acutely unwellRequire emergency treatmentAre identified by the ANC provider during pre-screening as having possible psychotic symptomsAre unable to understand the interview (e.g. diagnosed with severe intellectual disability or dementia, or unable to speak Amharic)Expect to move away from the study area before the study is completed

All women endorsing question nine of PHQ-9 about suicidal thoughts or self-harm behaviours will receive the Amharic [63] Mini-International Neuropsychiatric Interview suicidality scale [65]. Women scoring 17 or above on the Mini-International Neuropsychiatric Interview (indicating high suicide risk) will be excluded from participation as part of a stepped-care model [54]. They will be referred instead to a mental health-trained primary care worker who will employ mhGAP [55] criteria to assess for imminent risk of self-harm or suicide. Women assessed as being at imminent risk will be referred to a psychiatric nurse in the primary hospital for escalation of their care. The attendance of participants at referred appointments will be facilitated by the study, including any attendant transportation costs to access off-site services. Any psychotic symptoms and risks identified during the trial will be discussed with the project mental health professional and women will be referred for specialist mental health care if required. Women assessed as eligible to participate at the time of screening but who do not consent to take part will receive the same stepped mental health care model, depending on their symptoms and any imminent risks.

Otherwise eligible women reporting no past-year IPV exposure will be invited to participate in the separate, nested feasibility trial of standard PST for depression but will not be eligible for this study of PST-IPV.

